## Abstract

**Background:**

Increasing levels of physical activity (PA) and reducing sedentary time among adolescents during the school day is a pressing need. Emerging methodologies and strategies been shown to be effective in increasing PA levels and providing additional benefits for students, such us physically active lessons (PAL), active breaks (AB) and active recesses (AR). However, evidence concerning adolescents remains limited. This manuscript presents the methods and rationale of the MOVESCHOOL study, which aims was to examine the effects of a multicomponent school-based intervention during the school day on indicators of PA, sedentary time, health, executive functions and education in adolescents.

**Methods:**

A quasi-experimental study was conducted with the aim to involve a total of 800 students aged 12–14 years old from 11 schools (7th and 8th grade) in south-western Spain, five schools forming the intervention group and six schools forming the control group. The evaluation included two independent measurements: pre-intervention and post-intervention. The intervention lasted 29 weeks and consisted of a multi-component programme including a weekly PAL, two 5 min daily AB, and a daily AR. Primary outcomes included accelerometer-based PA and sedentary time, health-related physical fitness, academic indicators, and executive functions. For statistical analyses, descriptive, correlational, regression, and repeated measures ANOVA analyses will be applied. Additionally, qualitative data were gathered through semi-structured individual interviews and focus groups, and information will be evaluated with thematic analysis.

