**Figure 1 fig1:**
[figure not shown]
Flow diagram of study participants.

The recruitment process was designed to achieve 800 participants (400 per group), which guarantees to detect small sized effects with an *α* error of 0.001 and a power (1 − *β*) of 0.95, even with an experimental dropout rate of 15% (GPower 3.1.9.4, Düsseldorf, Germany). To establish this sample size, Love et al. (38) were referenced, as they found an average effect size <0.1 for our main variable, MVPA time during the school day.

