##### Physical activity and sedentary time

2.5.1.1

The Actigraph device (Actigraph GT3X+, Inc., Pensacola, FL, United States) was utilized for assessing PA at different intensities (light, moderate and vigorous) and sedentary time throughout the entire day. Participants were instructed to wear the monitor on their non-dominant wrist for eight consecutive days. Participants were advised to wear the accelerometer throughout the day (including sleeping time), except during aquatic activities or situations where exposure to water is possible. The screening and data collection procedures adhered to established protocols employed in previous research involving adolescents populations (42). Data will be extracted and analyzed using the GGIR package. Inclusion criteria for the analyses consist of: (i) a minimum of 3 valid weekdays of data and at least 1 valid weekend day of data; (ii) a minimum recording duration of 10 h per day (42, 43). The power analysis is performed based on MVPA during the school day, as it is the main variable of the study.

Additionally, to gather information on screen time throughout the day and the devices used, screen time was assessed using the specific items of the Youth Leisure-time Sedentary Behaviour Questionnaire (YLSBQ) (44). This questionnaire assessed the amount of recreational time per day spent on television, video games, computers, tablets, and smartphones, separately during weekdays and weekends. The student must choose whether they spend “0 min”, “30 min”, “1 h”, “2 h”, “3 h”, “4 h” or “5 h or more” per day on each of these behaviours.

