### Data analysis

2.6

Continuous variables will be presented as mean and standard deviation or median and interquartile range, as appropriate, while categorical variables will be expressed as frequency and percentage. A cross-sectional approach will be utilized, employing descriptive, correlational, regression, and differential analyses, along with Structural Equation Modeling. To evaluate the effects of the interventions on outcomes, repeated measures analysis will be conducted, with outcome measures serving as dependent variables in separate models, the intervention as an independent variable, and controlling for potential confounders (i.e., gender). Non-parametric analyses will be conducted if normality analyses indicate non-normal distributions. Quantitative analyses will be conducted using the SPSS v.29.0 statistical package (IBM, Armonk, NY, United States), with a confidence level of 95%.

Additionally, qualitative data from semi-structured interviews and focus groups will be analyzed using NVIVO software (61). Content analysis strategies will be employed, involving two phases: a deductive phase aimed at identifying information relevant to the study’s objectives, followed by an inductive phase focused on identifying teachers’ and students’ experiences, thoughts, and reflections related to AR, AB, and PAL (62).

To mitigate potential biases associated with the quasi-experimental design, we will apply statistical adjustments to control for confounding variables (i.e., gender, city, socioeconomic status) and ensure the robustness of our findings. Additionally, sensitivity analyses will be conducted to assess the impact of potential biases.

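### Repeated measures ANOVA with two waves analyses by default only students with both values; a mixed model using every student with a valid wave is the safer choice

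*Protocol article*

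**What the plan says.** The abstract lists the planned methods and ends with the statement that "repeated measures ANOVA analyses will be applied". Section 2.6 (Data analysis) is the place that ties a method to the intervention effect, and it is less specific: "To evaluate the effects of the interventions on outcomes, repeated measures analysis will be conducted", with one model per outcome and adjustment for confounders. It names the software: "Quantitative analyses will be conducted using the SPSS v.29.0 statistical package". There are two waves: "The evaluation included two independent measurements: pre-intervention and post-intervention".

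Two statements bear on how many students will have both values. In section 2.2 the sample size is said to suffice "even with an experimental dropout rate of 15" per cent. In section 2.5.1.1, accelerometer data enter the analyses only with "a minimum of 3 valid weekdays of data and at least 1 valid weekend day of data" and "a minimum recording duration of 10 h per day".

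The article states neither a complete-case rule nor an imputation method. Section 2.6 promises sensitivity analyses for potential biases but does not describe them.

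**The concern.** In SPSS, classical repeated measures ANOVA needs a complete row for each student. A student with a good baseline and no valid follow-up, or the reverse, is dropped. With two waves the group x time test is then the same as comparing mean change between groups among completers.

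Two things could be lost. One is information, because students with a single usable wave contribute nothing. The other is freedom from bias. If low-activity students are lost more often in one group than in the other, the completers in the two groups start from different baseline levels for that reason alone. Regression to the mean then appears as a difference in change. Allocation was not random, and only the intervention schools had a technician on site, so a different loss pattern by group is conceivable. The expected effect on the main variable is described as small, so even a modest bias would matter.

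**Working it through.** **Inputs from the documents.** 800 students; 15% dropout; two waves; 11 schools; wear rule for accelerometer outcomes.

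**Assumptions, not in the documents.** Pre-post correlation rho = 0.5; unit variance at each wave; invalid wear, strength of baseline-dependent loss and school ICC of change as varied below.

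**1. How many completers.** Dropout alone leaves 800 x 0.85 = 680. If a share u of the remaining students fails the wear rule at each wave, independently, completers number 680 x (1 - u)^2:

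| u | Completers |
|---|---|
| 0 | 680 |
| 5% | 614 |
| 10% | 551 |
| 20% | 435 |
| 30% | 333 |

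**2. Bias of the completer contrast, no true effect.** With baseline Y1 standardised, expected change given baseline is -(1 - rho) x Y1. The mean change among completers is therefore -(1 - rho) x E[Y1 | completer], and the bias is the difference of that term between groups. It is zero if loss is completely random, and zero if loss depends on baseline in the same way in both groups.

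Let loss follow a logistic model in Y1 with slope b in one group only, and let it be unrelated to Y1 in the other. The intercept is set to give the stated overall loss, and E[Y1 | completer] is found by numerical integration. Bias = 0.5 x |E[Y1 | completer]|:

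| Loss | b per SD | Size of E[Y1 given completer] | Bias (SD) |
|---|---|---|---|
| 15% | 0.2 | 0.030 | 0.015 |
| 15% | 0.5 | 0.073 | 0.036 |
| 15% | 1.0 | 0.133 | 0.066 |
| 30% | 0.2 | 0.060 | 0.030 |
| 30% | 0.5 | 0.143 | 0.071 |
| 30% | 1.0 | 0.253 | 0.126 |

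A separate simulation (400 per group, true effect 0.20 SD, about 30% of follow-up values missing) gave a completer average of 0.20 under random loss, 0.20 under equal baseline-dependent loss, and 0.085 under baseline-dependent loss in the intervention group only. The likelihood estimate from all available data stayed at 0.20 in all three.

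**3. Precision, schools ignored.** Let v be the share valid per wave, independent between waves. Completers are c = v^2; those with exactly one given wave are v(1 - v). Per enrolled student:

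- completer variance of mean change: 2(1 - rho)/c
- all-data variance: 2 / [c/(1 - rho) + v(1 - v)]

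At v = 0.8: c = 0.64, and 1 - 0.2^2 = 96% of students have at least one wave. Completers give 1/0.64 = 1.5625. All data give 2/(1.28 + 0.16) = 1.389. The ratio is 0.889, so variance falls by 11%. At v = 0.9 and 0.7 the ratios are 0.947 and 0.824.

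**4. Precision, schools included.** With 800/11 = 73 students per school and v = 0.8, completers per school are m = 0.64 x 72.7 = 46.5. The variance of a school's mean change is proportional to ICC + (1 - ICC)/m for completers. Using all data multiplies only the second term by 0.889:

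| ICC of change | Completers | All data | Reduction |
|---|---|---|---|
| 0.02 | 0.0411 | 0.0387 | 5.7% |
| 0.05 | 0.0704 | 0.0681 | 3.2% |
| 0.10 | 0.1193 | 0.1172 | 1.8% |

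**The case against.** The strongest reply is that this is a missing-data policy left to a fuller document. The article states no listwise rule, and section 2.6 uses wording that excludes neither a mixed model nor imputation before an ANOVA. The explicit term appears only in the abstract's list of methods. This stands in part: the completer analysis is the default consequence of the method named, not a declared policy. Still, ANOVA is the only specific repeated measures model the article names, and asking for a better one is not a complaint about omitted detail.

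A reader might infer that the completers will be a self-selected group and the estimate therefore biased. The documents do not support that. They give no missing-data rate by group, no pattern and no reasons, only a planning allowance and a wear rule. That on-site technicians would change the loss pattern is conjecture. Nor is it right that the ANOVA is unbiased only when loss is unrelated to the outcome: loss that depends on baseline equally in both groups does no harm.

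It is also tempting to set the bias against the average effect of under 0.1 cited in section 2.2. That figure has no stated metric, so the comparison with SD units is unsafe. Finally, the 11% variance figure assumes invalid wear is independent between waves. If the same students fail twice, the gain is smaller, in addition to the reduction from school clustering shown above.

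The promised sensitivity analyses might cover this, but nothing says that they do.

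**Conclusion.** The concern holds as a choice of method that can be improved cheaply, not as a demonstrated error in the results. As named, the analysis would by default rest on students with valid data at both waves, at most 680 of 800 under the plan's own dropout figure and fewer if invalid wear comes on top.

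The main reason to change is protection against bias if loss depends on baseline differently by group: roughly 0.015 to 0.07 SD at 15% loss and 0.03 to 0.13 SD at 30%, for slopes of 0.2 to 1.0 per SD in one group and a correlation of 0.5. Under other loss patterns the bias can be zero. The gain in precision is a secondary benefit. The change is worth making, with moderate rather than high confidence that the current wording would cause harm.

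**What to change.** In the abstract and in section 2.6, name the same model: a linear mixed model (SPSS MIXED, REML) in place of repeated measures ANOVA. Include group, time, group x time and the confounders already listed (gender, city, socioeconomic status), with student and school effects. Leave baseline means free by group, because allocation was not random. Include every student with at least one valid wave and take group x time as the intervention effect. Keep the complete-case analysis as one of the sensitivity analyses already promised.

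The cost is a change of wording and slightly more modelling in software already chosen; no new data are needed. The model relies on missing at random, which cannot be verified. It is nevertheless weaker than what the completer analysis needs, since it allows loss to depend on observed values differently in each group.

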**Discussion:**

The MOVESCHOOL study represents a pioneering effort in Spain, being the first of its kind to evaluate the effectiveness of a multicomponent programme in secondary schools. Furthermore, this project provides valuable insights into the effects of a multicomponent school-based PA intervention on PA levels, sedentary time, health-related, cognitive, academic indicators and psychological health markers in secondary school students. The results of this study will make a significant contribution to the educational community, providing them with innovative teaching methods and strategies that have the potential to increase PA levels during the school day. In addition, this research promises to provide a transformative experience for educators, equipping them with tools to promote the holistic development of their students, enriching their academic performance and enhancing their well-being.

**Clinical trial registration:**

ClinicalTrials.gov, identifier NCT06254638.

## Introduction

1

Increasing levels of physical activity (PA) and reducing sedentary time among children and adolescents is of paramount importance, as it helps to address the problems associated with current and lifelong physical inactivity, such as obesity and overweight (1–3). Additionally, it can positively affect other important factors during this stage, such as cognition and academic performance (4). Currently, PA levels among school-aged children are concerning. A systematic review in participants aged 5 to 18 years showed that children (≤12 years) spent 41 to 51% of the after-school period in sedentary time, whereas adolescents (>12 years) spent 57% of the after-school period in sedentary time (5). In addition, the school day is usually sedentary and Grao-Cruces et al. (6) found that Spanish secondary school students spent an average of 78% of the school day in sedentary behaviour.

Of all the contexts in which PA can be promoted at these ages, educational institutions have been identified as the most appropriate setting for intervention (7, 8). This is based on the fact that all children and adolescents have to spend a significant part of their waking hours at school, during crucial periods for the acquisition and consolidation of life habits. The presence of university-trained professionals in various fields and greater access to families also facilitates the role of these institutions as health promoters. In line with this, Spanish education legislation stipulates that schools should promote PA during the school day and encourage healthy lifestyles among their students (9).

Recently, World Health Organization (WHO) (8) published a policy brief toolkit describing the importance of integrating PA into schools. Among other things, to ensure that children aged 5 to 17 meet the recommendation of achieving 60 min of moderate to vigorous PA (MVPA) per day. In addition, the Sedentary Behaviour Research Network (SBRN) described the international evidence-based recommendations for school-related sedentary behaviour for youth (10), recommending that long periods of sedentary behaviour should be interrupted, that different types of PA should be incorporated, and that sedentary and screen-based learning activities should be replaced by active and non-screen-based learning activities. Therefore, in light of the recommendations from WHO and SBRN, there is a need to establish “active schools.”

Over the past decade, there has been a growing interest in developing viable strategies to increase PA levels throughout the school day without reducing time for other subjects. In this context, the scientific literature highlights the following strategies: physically active lessons (PAL), active breaks (AB), and active recess (AR). PALs are academic lessons other than PE (e.g., maths) that incorporate PA during teaching-learning activities without reducing the time devoted to the content of those subjects (11). These are based on integrating movement through exercises and games into areas other than PE to teach new academic content without compromising educational time (12, 13). A systematic review by Daly-Smith et al. (14) found that interventions combining PA with academic content showed higher levels of PA, time on task and academic outcomes, although this is less well established for adolescents. However, the evidence is not clear regarding some variables, such as changes in health-related physical fitness (HRPF) (13, 15, 16) or cognitive functions (13), as there are studies reporting significant effects and others that do not. Moreover, this lack of clarity is exacerbated in secondary education, where the existing evidence is more limited (13, 14). Therefore, further research in this area is necessary.

AB involves short bouts of PA, often of MVPA intensity, delivered by teachers during or between curricular lessons (12). Previous studies (12, 14, 17) have shown that AB significantly improves PA levels, but the results are inconclusive regarding the benefits on cognitive function and classroom behaviour. Once again, few studies have evaluated the effectiveness of AB in secondary education (14, 17). Specifically, at this stage, it has been demonstrated that 4 min AB are sufficient to achieve significant improvements in cognition (18). Although the duration of AB (ranging from 4 to 10 min) was consistent across studies, variations were observed in the frequency of application [ranging from two (19) to four (18) per school day].

Recess during the school day can be defined as “the non-curricular time scheduled between lessons” (20), and usually involves access to outdoor spaces and provides students with opportunity for unstructured PA and to socialize with their peers (21). Recess is a time with potential to contribute up to 40% of the daily MVPA recommendations (22). Therefore, AR can be described as recess that provides opportunities for students to engage in PA during school day (23). Previous studies (24, 25) reported that PA during recess can lead to improvements in academic, cognitive, behavioral, and emotional indicators.

This project was based on the framework of the Creating Active Schools (CAS) model (26). Based on the Behaviour Change Wheel (BCW) (27), the CAS models identified three sources of behaviour that are necessary and sufficient for the performance of a given volitional behaviour: Capability, Motivation and Opportunity. Furthermore, this model classified several intervention functions that could enable interventions (i.e., education, persuasion, empowerment, training, modeling, or constraints), as well as several target groups to develop the intervention. In this way, the CAS model framework identifies the multiple components necessary to establish schools as adaptive complex subsystems, which in turn facilitate the implementation of PA throughout the school. The lower half of the framework describes the internal factors of the school, while the upper half identifies factors related to teacher training, behavioral science, and the role of national and international organisations and policy development—the wider system beyond the individual school. In our project we focused on: (i) school leaders, who are responsible for leading the development of policy and vision statements and managing related resources; (ii) teachers, who are central to creating a positive social and physical environment, as well as implementing initiatives to promote healthy lifestyles; and (iii) students, who may form student councils or lead opportunities to adopt healthy lifestyles. By intervening with these groups, strategies to increase PA levels during the school day were developed and implemented through three opportunities (i.e., PAL, AB and AR).

Analyzing previous studies on interventions for promoting PA in schoolchildren (28–32), it is observed that a large part of these implement a single PA component (e.g., only PAL). Most single-component interventions in schools have shown limited or insignificant post-intervention effects (31, 32). Additionally, the possible low quality of existing systematic reviews, meta-analyses, or the studies included in them limits the ability to draw firm conclusions (32). Despite the limited evidence, multicomponent school-based interventions (targeting two or more components, such as PAL, AB, active commuting, etc.) have been proposed as one of the most promising approaches to promote PA in schools (32–35). However, systematic and meta-analyses examining the effects of multicomponent interventions show inconclusive results and generally small effects (36, 37). Evidence for these types of interventions on variables such as executive functions or academic performance is weak.

On the other hand, most of these multicomponent interventions have been carried out in primary schools (32), and few in secondary stage, with inconclusive effects on PA levels (36, 37). Therefore, there is a need to conduct studies that focus on the secondary level and test multicomponent interventions, as they promise greater effects on PA levels, and all that this entails.

Starting from the fact that this work is a protocol, its aim was to describe the methods and rationale of the MOVESCHOOL study, aimed to examine the effectiveness of a multicomponent school-based intervention on PA levels, sedentary time, HRPF, executive functions, academic indicators (school engagement, learning perception, academic performance and mathematical fluency), psychological health markers and motivational variables in adolescents. A secondary objective was to describe the methods used to evaluate the perception of school leaders, teachers and students (perceptions, limitations, strengths, areas for improvement, perceived benefits, enjoyment, motivation, training needs, fidelity and sustainability) about the intervention. Based on previous studies, this study hypothesized that participants in the experimental group, compared to those in the control group, would show higher PA levels during the school day, improved HRPF, executive functions, academic performance, psychological health, and motivation, as well as a reduction in sedentary time during the school day.

